### Biochemistry

At each clinic visit, 20 mL of non-fasting, whole blood will be taken from the median cubital vein and collected into an ethylenediaminetetraacetic acid (EDTA)-coated tube. Plasma carotenoids, including lycopene, lutein, β-cryptoxanthin, α-carotene, and β-carotene will be analyzed using high-performance liquid chromatography [51]. Plasma inflammatory markers (IL-1, IL6, TNF-α) will be measured using standard ELISA assay procedures (Cayman Chemical, Ann Arbor, MI, USA). Total antioxidant potential will be measured using calorimetric assay (Sapphire Bioscience, Waterloo, NSW, Australia). Plasma zinc will be measured using atomic absorption spectrometry. Erythrocyte superoxide dismutase activity will be measured by colorimetric assay (Bioxytech; OXIS International, Portland, OR, USA). Total fatty acids in red blood cell membranes will be analyzed by gas chromatography [52].

### Achieving compliance

Compliance with the intervention is critical to the success of this project and will be achieved using behavior change strategies including self-monitoring, and regular phone calls for dietary counseling. The $30 shopping voucher will be used to assist compliance as this population typically has a low intake of antioxidant-rich foods. All participants will complete a food group diary and regular 24-hr dietary recalls, and the intervention group will have additional dietary education during the phone calls. We have previously achieved good compliance with this intervention using similar strategies [10,11]. To monitor compliance, we will measure blood carotenoids for the increased fruit and vegetable consumption. We will also collect the shopping voucher receipts and document amounts of foods purchased.

### Randomization

The randomization schedule will be created by an independent statistician using ralloc.ado version 3.6.1 in Stata version 11.1. Randomization will be stratified by pre-pregnancy asthma severity (based on the Global Initiative for Asthma guidelines) and body mass index.

### Sample size and recruitment

The primary outcome for this study is asthma control (ACQ6). In our previous study, we saw a change in asthma control of 0.4 (SD = 0.9) following 10 days on a low-antioxidant diet [10]. In this trial of longer duration we expect to see a clinically significant change in ACQ of 0.5. Using PS.exe (Power and sample size calculation, version 3.0.43) with two-tailed *t*-tests at 80% power, we have determined that a sample size of 52 completions per group is required. The previous trial achieved 78% retention; however, 20% were removed from the analysis due to non-compliance. Therefore, we will recruit 168 women so that 104 women (52 per group) will complete the study and be included in the analysis. There are 3,600 births per year at LMH and at least 12% of the women have asthma. From our previous cohort studies at the LMH, we have found that approximately 360 pregnant women have a complication of asthma. We will need to recruit a minimum 84 per year (including 20% low compliance + 22% drop out) to complete the study within 3 years. We believe capturing this number of women per year is feasible, given we only need to recruit 23% of the asthmatic women presenting to the Antenatal Clinic.

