**Methods/design:**

A 12 week, parallel randomized controlled trial will be conducted. One hundred and sixty eight pregnant women with mild, moderate, or severe asthma, currently using inhaled corticosteroids, and with poor diet quality, will be recruited at approximately12 weeks gestation. Following a 4 week run-in period, women will be randomized to either a 12 week antioxidant intervention (increased consumption of antioxidant-rich foods (≥5 servings/day vegetables, ≥2 servings/day fruit, ≥8 ½ servings/day grains (mostly wholegrains), 3–4 serving/week lean meat) or standard pregnancy care. The primary outcome is asthma control score (decrease of 0.5, the minimally clinically significant change). Secondary outcomes include plasma antioxidants, markers of oxidative stress, and time to, and number of, exacerbations. With two-tailed t-tests at 80% power, a sample size of 52 completions per group is required. Allowing for a 78% retention including a 20% removal of women from the analysis due to non-compliance, we will recruit 168 women.

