### Statistical analyses

All statistics will be performed using SPSS version 20.0 (SPSS, Inc., Chicago, IL, USA). Frequencies and descriptive data for the study population will be reported as mean (SD) or between groups as mean (± standard error of the mean). Prior to hypothesis testing, the distribution of the data will be examined for normality. Any skewed data will be natural log-transformed. Outcome comparisons will be made according to the treatment allocation at randomization on an intention-to-treat basis. Both adjusted and unadjusted analyses will be carried out. Continuous variables with repeated measurements (that is, ACQ6 score, blood results) will be analyzed using a generalized linear mixed model with a random intercept for individuals, to account for repeated measurements. Planned sub-analyses will be undertaken to assess the effects of asthma severity, asthma control, forced expiratory volume in 1 second (FEV_1_) and F_E_NO, on the primary and secondary outcomes. We will account for changes in ICS by assessing ICS intake as a cumulative dose over the study period. Differences between groups in time to exacerbation will be analyzed using Kaplan-Meier curves. All tests will be conducted two-sided, and a *P*-value <0.05 will be considered statistically significant.

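### The sample size assumes that 20% of women are removed from the analysis for non-compliance, but the analysis section specifies intention-to-treat, so the stated 80% power belongs to a different analysis set

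*Protocol article*

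**What the plan says.** The sample-size section takes two losses from an earlier trial by the same group: 78% retention, and 20% removed from that trial's analysis for non-compliance. It carries both into this trial: "Therefore, we will recruit 168 women so that 104 women (52 per group) will complete the study and be included in the analysis". The same section lists 20% low compliance and 22% dropout together when it gives the yearly recruitment target. The abstract states the removal as part of this trial's own plan: "Allowing for a 78% retention including a 20% removal of women from the analysis due to non-compliance, we will recruit 168 women". Table 1 shows 168 women at the week-14 run-in and 104 at week 30.

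The basis for the 52 is given as "at 80% power, we have determined that a sample size of 52 completions per group is required", with the target "In this trial of longer duration we expect to see a clinically significant change in ACQ of 0.5" and an SD of 0.9 from the earlier study.

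The statistical analysis section gives a different rule: "Outcome comparisons will be made according to the treatment allocation at randomization on an intention-to-treat basis". It names no per-protocol or compliers-only analysis to which the removal could belong. On adherence, the section on achieving compliance says: "To monitor compliance, we will measure blood carotenoids for the increased fruit and vegetable consumption". It also says that shopping-voucher receipts will be collected.

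**The concern.** A retained woman who does not follow the diet cannot be both analysed in her allocated group and removed from the analysis. An analyst could follow either statement and cite the protocol in support, and the choice decides who enters the primary comparison.

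Two things are at stake. First, the power statement. If intention-to-treat is followed, the non-compliers stay in, which raises the number analysed but may shrink the expected difference. The protocol gives neither the resulting number nor an effect that allows for the non-compliance it expects. Second, validity. If the removal is carried out, women are selected on something that happens after randomization. Only the intervention group receives vouchers and dietary counselling, so removal could well differ between the groups, and the comparison would then no longer be protected by randomization.

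**Working it through.** **Inputs.** Difference 0.5, SD 0.9, 80% power, 52 per group, 78% retention and 20% removal are from the sample-size section. The two-sided test at 0.05 is from the statistical analysis section ("All tests will be conducted two-sided"; P "<0.05 will be considered statistically significant").

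**Step 1: reproduce the 52 per group.** Normal approximation: n = 2 x (1.96 + 0.842)² x 0.9² / 0.5² = 50.9, so 51. The exact two-sample t-test (noncentral t) needs 52 per group, with power 80.1%; 51 per group gives 79.3%. The stated figure is reproduced.

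**Step 2: reproduce the 168.**

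| Losses assumed | Calculation | Women to recruit |
|---|---|---|
| Dropout, then removal of non-compliers | 104 / (0.78 x 0.80) = 166.7 | 167 |
| Both losses added | 104 / (1 - 0.42) = 179.3 | 180 |
| Dropout only | 104 / 0.78 = 133.3 | 134 |

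Only the first row comes close to 168. Forward, 168 x 0.78 x 0.80 = 104.8. The removal is therefore built into the recruitment figure. Table 1's 104 at week 30 is the number after removal; retention alone leaves 168 x 0.78 = 131.

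**Step 3: power under the stated analysis.** With non-compliers kept, 131 / 2 = 65.5 per group. The noncentrality is d / (0.9 x √(2/65.5)). The protocol gives no intention-to-treat effect, so a range is shown.

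| Intention-to-treat difference | Basis | Noncentrality | Power |
|---|---|---|---|
| 0.50 | no dilution | 3.18 | 88% |
| 0.45 | 20% of the intervention group gain half: 0.5 x 0.90 (assumed) | 2.86 | 81% |
| 0.40 | 20% gain nothing: 0.5 x 0.80 (assumed) | 2.54 | 71% |

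Power stays at 80% or more down to a difference of about 0.44.

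An upper bound comes from the mixed model using partial data. If it recovered full information from all 168 women (84 per group), power at 0.40 would be 82%. That cannot be fully reached, because the 168 are counted at run-in, before randomization at week 18.

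**Step 4: could removal bias the result?** This is an illustration only: 65 per group, no true effect, and the 20% with the greatest tendency to non-compliance removed.

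- Removed from the intervention group only, with an assumed correlation of 0.3 to 0.5 between non-compliance and worse ACQ6: a spurious benefit of about 0.09 to 0.16 points, and a type I error of about 8% to 16%.
- The same one-sided removal with a correlation of 0.1: type I error about 5%.
- Equal removal from both groups by the same mechanism: bias about zero, and type I error about 5% to 6% at correlations of 0.3 to 0.5.

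The result depends entirely on the assumed pattern of removal and the assumed correlation, neither of which is in the protocol.

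**The case against.** The strongest reply is that intention-to-treat is the only rule the article gives for comparing the groups. On this view the 20% is past experience from another trial, used as a recruitment allowance, and no Methods passage sets out a deletion rule. This stands in part: if the analysis section is followed, randomization is intact. But the abstract speaks of removal from the analysis as this trial's plan, and the sample-size section counts only 104 women as analysed. An allowance that leaves women in the analysis would not reduce the number to 104.

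A second reply is that 0.5 is described as the minimally clinically significant change. Read as the target between-group difference, it needs no dilution, and keeping non-compliers lifts power to 88%. This also stands. A reader might infer that the intention-to-treat analysis must be underpowered, and the documents do not support that: power falls below 80% only if the difference drops below about 0.44.

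Three other stronger readings are tempting and go too far.

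- That the primary result will be biased towards the diet. The sample-size text plans 52 in each group, so its allowance is equal. Food diaries, recalls and blood samples are collected in both groups. Neither one-sided removal nor its link with ACQ6 can be derived from the document.
- That women with low carotenoids will be deleted, which would help produce the result on antioxidant concentrations. Carotenoids are named as a way of monitoring compliance, not as an exclusion criterion.
- That the lack of a definition of non-compliance is itself an error. A condensed article may leave that to the full protocol or SAP.

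**Conclusion.** The conflict is real and lies in the current text. The 168, the 104 and the 80% power all rest on taking non-compliers out of the analysis, while the analysis section keeps every woman in her allocated group. The arithmetic is right for a compliers-only set; the mismatch is in who is analysed.

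Under the stated intention-to-treat analysis, the expected number with week-30 data is about 131 and power is about 71% to 88% for a difference of 0.40 to 0.50. This rests on SD 0.9, 78% retention applied to the 168, a t-test on week-30 data, and dilution values that are assumptions. A mixed model using partial data may do somewhat better.

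If the removal were carried out, it would select on a post-randomization variable and could bias the comparison, especially if it differed between groups. The document supports no figure for that bias, and the simulated values show only that it need not be negligible.

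**What to change.** 1. Delete the removal for non-compliance from the abstract and the sample-size section, including the 20% low-compliance allowance in the recruitment target. State that all randomized women are analysed in their allocated group.
2. Restate the size as 168 recruited at run-in, with about 131 expected to have week-30 data at 78% retention. Change Table 1 from 104 to match. Do not describe the 168 as randomized, since Table 1 counts them four weeks before randomization.
3. Replace the single power figure with a range: about 88%, 81% and 71% at intention-to-treat differences of 0.50, 0.45 and 0.40, noting that the two smaller differences are assumptions about dilution.
4. If a compliers-only analysis is wanted, label it secondary.

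The cost is wording only, and the article gives the trial status as not yet recruiting. The stated power becomes a range that depends on assumed dilution. The correction itself needs no more women. If the sponsor wished to guarantee 80% power at a difference of 0.40, that would be a separate decision: 81 per group, or 162 / 0.78 = 208 recruited.

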### Statistical analyses

All statistics will be performed using SPSS version 20.0 (SPSS, Inc., Chicago, IL, USA). Frequencies and descriptive data for the study population will be reported as mean (SD) or between groups as mean (± standard error of the mean). Prior to hypothesis testing, the distribution of the data will be examined for normality. Any skewed data will be natural log-transformed. Outcome comparisons will be made according to the treatment allocation at randomization on an intention-to-treat basis. Both adjusted and unadjusted analyses will be carried out. Continuous variables with repeated measurements (that is, ACQ6 score, blood results) will be analyzed using a generalized linear mixed model with a random intercept for individuals, to account for repeated measurements. Planned sub-analyses will be undertaken to assess the effects of asthma severity, asthma control, forced expiratory volume in 1 second (FEV_1_) and F_E_NO, on the primary and secondary outcomes. We will account for changes in ICS by assessing ICS intake as a cumulative dose over the study period. Differences between groups in time to exacerbation will be analyzed using Kaplan-Meier curves. All tests will be conducted two-sided, and a *P*-value <0.05 will be considered statistically significant.

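### The log-transformation rule exempts no outcome, so it could turn the primary ACQ6 effect into a ratio although the trial defines and sizes it as a 0.5-point difference

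*Protocol article*

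**What the plan says.** The Statistical analyses section sets out a two-step rule: "Prior to hypothesis testing, the distribution of the data will be examined for normality", and then "Any skewed data will be natural log-transformed". It lists no outcomes to which the rule is limited. The same section names the ACQ6 score, together with the blood results, among the continuous repeated measures to be analysed in a mixed model with a random intercept per woman.

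The primary outcome is expressed in points. The abstract (Methods/design) says: "The primary outcome is asthma control score (decrease of 0.5, the minimally clinically significant change". Sample size and recruitment says "The primary outcome for this study is asthma control (ACQ6" and adds that "we expect to see a clinically significant change in ACQ of 0.5". The variability comes from an earlier study on the same raw scale: "we saw a change in asthma control of 0.4 (SD = 0.9) following 10 days on a low-antioxidant diet". The calculation is reported as "with two-tailed *t*-tests at 80% power, we have determined that a sample size of 52 completions per group is required".

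The abstract also lists secondary outcomes: "Secondary outcomes include plasma antioxidants, markers of oxidative stress, and time to, and number of, exacerbations". Statistical analyses gives Kaplan-Meier curves for time to exacerbation.

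**The concern.** A log transformation changes what is estimated. The difference between arms on the log scale back-transforms to a ratio of geometric means, not to a difference in points. If the rule were triggered for ACQ6, the primary result would no longer be on the scale on which the trial defines a clinically meaningful change and on which it was sized. That choice would also be made after looking at the outcome data.

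The trigger is poorly aimed as well. A mixed model with normal errors makes assumptions about residuals and random effects. It does not require the raw scores to be normal, so skewed raw ACQ6 scores are not in themselves a reason to change scale.

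A second problem arises at the bottom of the scale. The Asthma control section defines controlled asthma as a score below 0.75 and gives no positive floor. If 0 can be scored, its logarithm does not exist. A diet that works would produce more such scores in the intervention arm, so the missing observations would depend on outcome and differ by arm.

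**Working it through.** **1. The plan's own figure.** Inputs from Sample size and recruitment: difference 0.5, SD 0.9, power 80%, two-sided; alpha 0.05 from Statistical analyses.
- Normal approximation: n = 2 × (1.960 + 0.842)² × (0.9/0.5)² = 2 × 7.85 × 3.24 = 50.9, so 51 per group.
- Exact two-sample t-test (noncentral t): 52 per group, power 80.1%.

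The stated 52 is reproduced on the raw points scale. No log-scale equivalent can be derived, because the article gives neither a mean ACQ6 nor a log-scale SD.

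**2. What 0.5 points means as a ratio.** For a starting score b, the ratio is (b − 0.5)/b. Conversely, a fixed ratio of 2/3 corresponds to b × (1 − 2/3) points.

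| Score b | Ratio for a 0.5-point fall | Natural log | Points for a ratio of 2/3 |
|---|---|---|---|
| 0.75 | 0.33 | −1.10 | 0.25 |
| 1.0 | 0.50 | −0.69 | 0.33 |
| 1.5 | 0.67 | −0.41 | 0.50 |
| 2.0 | 0.75 | −0.29 | 0.67 |
| 3.0 | 0.83 | −0.18 | 1.00 |

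No single ratio matches 0.5 points. This step needs no assumption about zeros.

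**3. Adding a constant does not settle it.** With ln(x + c), a fall from 1.0 to 0.5 gives (0.5 + c)/(1.0 + c). For illustration, c = 0.1 gives 0.6/1.1 = 0.55 and c = 1 gives 1.5/2.0 = 0.75. The effect measure depends on the constant chosen.

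**4. If zeros occur and are dropped (assumption).** If zeros were equally common in both arms, with effect and SD unchanged, 5%, 10%, 20% or 30% zeros would leave 49, 46, 41 or 36 women per arm at one time point. Power would be 77.7%, 75.0%, 70.0% or 64.2%.

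Equal loss is unlikely if the diet works. A simulation therefore used 52 women per arm, one time point, gamma-distributed scores with SD 0.9, rounded to sixths and limited to 0 to 6, and a true difference of 0.5. All distributional features are assumed.

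| Control mean | Zeros, control vs intervention | Difference among non-zero scores | Power, raw points | Power, log with zeros dropped |
|---|---|---|---|---|
| 1.0 | 5% vs 44% | 0.17 | 82% | 35% |
| 1.25 | 1% vs 18% | 0.35 | 81% | 78% |
| 1.5 | 0.1% vs 5% | 0.45 | 79% | 92% |
| 2.0 | almost none | 0.50 | 80% | 92% |

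The damage is severe near a control mean of 1.0. By 2.0 the zeros no longer matter.

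**5. Exacerbation counts.** Under an assumed Poisson mean of 0.2, 0.35, 0.5 or 1.0 per woman, the share with a count of zero is exp(−mean) = 82%, 70%, 61% or 37%. A literal logarithm is not usable for such an outcome.

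**The case against.** The rule is conditional, and nothing in the article shows that ACQ6 will be skewed. Some text points the other way: Asthma management and education describes asthma at this hospital as often poorly controlled, and Participants excludes intermittent asthma. Where the mean score is higher, the simulation shows the log analysis with more power, not less. The rule is sensible for the carotenoids and inflammatory markers under Biochemistry. The skewness criterion, the handling of zeros and back-transformation are details that an article may leave to the analysis plan. Group means with standard errors are also to be reported, and a marginal difference in points could be recovered from a log model if someone specified it.

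Most of this stands, and it rules out several stronger readings that a reader might infer:
- **That ACQ6 will be log-transformed.** The document supports only that it could be.
- **That zeros will be deleted.** This follows from a literal logarithm with no constant. The article does not plan it.
- **That 17 to 50 women would lose their primary data** (an assumed 10% to 30% of 168). Table 1 places the 168 at run-in, before randomization; the same rates on 104 completers give 10 to 31. ACQ6 is scheduled seven times from baseline to week 30, so a zero would cost that visit's value, not the woman.
- **That the log analysis weights milder women almost four times as heavily.** The ratio 0.69/0.18 = 3.8 shows how one absolute change looks in logs at two starting scores. It is not a statistical weight.
- **That the lack of a named count model is itself an error.** That is mainly detail left out of an article. The point is only that the stated rule, read literally, extends to counts.

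The objection does not remove the mismatch of scale. The scope of the rule is stated text, it includes the primary outcome, and a ratio is not the quantity on which the trial was sized. Higher power for a ratio does not answer a question posed in points.

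**Conclusion.** The concern holds in a limited form. The rule is unrestricted and triggered by the data. If it is triggered for ACQ6, the primary effect moves from a 0.5-point difference to a ratio that corresponds to 0.5 points at only one starting score (0.50 from 1.0, 0.83 from 3.0). This part rests on the article's text and arithmetic alone.

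The loss of zero scores is a further risk. It depends on four things that the article does not establish: that the scores are judged skewed, that 0 is attainable, how often it occurs, and that no constant is added. Its effect runs from serious at an assumed control mean of 1.0 to negligible at 2.0. The stated sample size is correct and unaffected. The wording should be changed, but the flaw does not undermine the design.

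**What to change.** Amend the Statistical analyses section in three respects.
- Analyse ACQ6 untransformed in the planned mixed model whatever its raw distribution, and report the between-group difference in points with a 95% CI. Check model residuals. As a sensitivity analysis, give a bootstrap CI that resamples women rather than visits.
- Restrict the natural-log rule to strictly positive laboratory concentrations.
- State that the rule does not apply to the number of exacerbations, and analyse that outcome with a count model, such as negative binomial regression with log follow-up time as the offset.

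The cost is a few sentences of analysis wording. No extra women or data are needed, and 52 completers per group still gives 80.1% power on the raw scale. The Trial status section says recruitment has not begun, so the change can be made before any outcome data are seen.

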### Protocol

At approximately 12 weeks gestation (range 10 to 14 weeks), asthmatic women will be recruited to participate (Figure 1) in the 12-week intervention study, with an initial 4-week run-in period (Table 1). At this initial visit, women will have the study procedures explained and have their asthma assessed (described below). A telephone call to determine consent will be made at approximately 13 weeks gestation in which a date to start the subsequent run-in period will be made. Signed consent forms will be obtained at the 14 weeks gestation visit. At this visit, the run-in period will commence where the women will be provided individual asthma management and education, complete a questionnaire on how/if their food intake has changed since learning they were pregnant, and will complete a food frequency questionnaire (FFQ). At 18 weeks gestation (that is, the baseline visit), women will be randomized into a control or intervention group (Table 1). At this baseline visit, weight and blood pressure will be measured, a fetal scan performed, questionnaires on asthma control, physical activity, and smoking will be completed, a blood sample taken, and dietary information collected. The same measurements will occur at 24 and 30 weeks gestation for all women. Phone calls will be made at 20, 22, 26 and 28 weeks gestation for information on asthma control and dietary intakes, and women in the intervention group will receive additional dietary counseling and support regarding the consumption of antioxidant-rich foods. At 30 weeks gestation, both groups will come back to the clinic for their final visit (Table 1). At delivery, birth outcomes will be assessed.

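### The random intercept is the only covariance term named for the seven ACQ6 scores, and it may understate the standard error of the 12-week change on which the trial is sized

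*Protocol article*

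**What the plan says.** Three parts of the protocol article bear on this.

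- **Analysis.** Under Statistical analyses, continuous outcomes measured repeatedly, with ACQ6 and blood results given as the examples, "will be analyzed using a generalized linear mixed model with a random intercept for individuals, to account for repeated measurements". The random intercept is the only device named for handling the repetition.
- **Schedule.** Under Protocol, baseline and randomisation are at 18 weeks, with clinic visits at 24 and 30 weeks. "Phone calls will be made at 20, 22, 26 and 28 weeks gestation for information on asthma control and dietary intakes". Table 1 lists ACQ6 at all of these contacts, which makes one baseline score and six later ones. The article does not say whether the telephone scores enter the primary model.
- **Sample size.** Under Sample size and recruitment, in an earlier study "we saw a change in asthma control of 0.4 (SD = 0.9) following 10 days on a low-antioxidant diet". The section continues: "In this trial of longer duration we expect to see a clinically significant change in ACQ of 0.5". The Abstract gives the result: "With two-tailed t-tests at 80% power, a sample size of 52 completions per group is required".

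**The concern.** The trial is sized on one change score per woman. The analysis is a model of up to seven scores per woman, with a covariance assumption that matters for exactly that change.

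A random intercept with independent residuals implies the same correlation between any two scores. A fortnightly symptom score is likely to behave differently. The article itself tracks colds, exacerbations and changes in inhaled corticosteroid, all of which act for a limited time and would make neighbouring scores more alike than distant ones. In that case the model borrows its residual variance from pairs of scores close in time and applies it to the most distant pair, weeks 18 and 30. The standard error is then too small and the false-positive rate on the primary test rises above 5%.

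A second question is which coefficient is read. An average over the follow-up scores is a different quantity from the difference at 12 weeks unless the effect is present early.

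**Working it through.** **Inputs from the article:** difference 0.5, SD of change 0.9, 52 per group, two-sided 5% level, ACQ6 at weeks 18 to 30 every fortnight. **Assumed, because the article gives neither:** how correlation depends on lag, and how the effect develops over time.

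**Step 1. The plan's own figure.** The normal approximation gives 2 × (1.96 + 0.8416)² × 0.9² / 0.5² = 50.9, so 51 per group. The exact noncentral-t calculation gives 79.3% power at 51 and 80.1% at 52. The stated 52 per group is reproduced.

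**Step 2. Standard error of the week 18-to-30 change.** Take m visits, a common variance σ² and a model with group by categorical visit.

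- The random-intercept model estimates the residual variance as σ²(1 − mean pairwise correlation), so its variance for one woman's change is 2σ²(1 − mean correlation).
- The true variance is 2σ²(1 − first-to-last correlation).
- Model SE / true SE = √[(1 − mean correlation) / (1 − first-to-last correlation)].
- Actual type I error ≈ 2Φ(−1.96 × ratio).

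Seven scores:

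| Assumed correlation | Mean | First to last | SE ratio | Type I error |
|---|---|---|---|---|
| Constant 0.5 | 0.500 | 0.500 | 1.00 | 5.0% |
| AR(1) 0.5 per fortnight | 0.239 | 0.016 | 0.88 | 8.5% |
| AR(1) 0.7 | 0.438 | 0.118 | 0.80 | 11.8% |
| AR(1) 0.8 | 0.581 | 0.262 | 0.75 | 14.0% |
| AR(1) 0.9 | 0.764 | 0.531 | 0.71 | 16.4% |
| AR(1) 0.95 | 0.875 | 0.735 | 0.69 | 17.8% |
| Linear fall 0.7 to 0.4 | 0.600 | 0.400 | 0.82 | 11.0% |

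For example, at AR(1) 0.9: √(0.236 / 0.469) = 0.71, and 2Φ(−1.96 × 0.71) = 16.4%. Simulation with 20,000 runs gave 5.1% (constant), 14.1% (AR(1) 0.8), 16.6% (AR(1) 0.9) and 11.0% (linear fall).

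If only weeks 18, 24 and 30 are used, AR(1) of 0.6, 0.8 and 0.9 per fortnight gives ratios of 0.94, 0.88 and 0.85, and type I errors of 6.6%, 8.5% and 9.7%.

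**Step 3. Reading an averaged effect instead.** Consider the mean of the six post-baseline scores minus baseline, with the SD of the week 18-to-30 change held at 0.9, 52 per group and correct standard errors.

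- *Linear rise to 0.5 at week 30.* The average is 0.5 × (2 + 4 + 6 + 8 + 10 + 12) / (6 × 12) = 0.292. Under constant correlation, σ²(1 − ρ) = 0.81 / 2 = 0.405, the variance of the averaged change is 0.405 × 7/6 = 0.4725, and the SE is √(2 × 0.4725 / 52) = 0.135. Power is Φ(0.292 / 0.135 − 1.96), about 58%. Under the AR(1) structures above it is 61% to 71%. The plan is 80%.
- *Early effect, 0.4 at week 20 rising evenly to 0.5.* The average is 0.45. Under constant correlation power is Φ(0.45 / 0.135 − 1.96), about 92%, and it is higher under the AR(1) structures.
- *Constant 0.5 from week 20.* The average is 0.5 and power is 96% to 99%.

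The averaged contrast is not immune to the covariance problem. Under the same AR(1) structures its random-intercept type I error is about 7% to 12%.

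**The case against.** The strongest reply is that this is a condensed article. Fixed effects, baseline handling and the named contrast are commonly left to a full protocol or SAP, and neither is shown. The article also signals its target through the 12-week aim, the 0.5 change and week 30 marked as the end. That stands: the absence of a stated contrast is not an error in itself, and nothing shows that the choice will be made after seeing the data.

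It is also true that the article does not call the random intercept the sole covariance term, does not list the visits in the model, and gives no correlations. With constant correlation there is no inflation. The only onset figure tied to the sample size, a 0.4 change at 10 days, points towards an early effect rather than a linear rise, although it comes from withdrawing antioxidant-rich foods rather than adding them.

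A reader might therefore infer that the analysis must either dilute the effect or inflate the false-positive rate. The documents do not support that: with constant correlation and an early effect, analysed as change from baseline, neither happens. A reader might also infer a much larger power loss by supposing that a group term pools the baseline score with the rest. The article never proposes that analysis.

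What the reply does not remove is that the article itself names a random intercept as the way to account for repetition. A fuller document that kept only that term would inherit the problem.

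**Conclusion.** The point holds as a conditional one. The covariance choice that the article states may understate the standard error of the comparison for which the trial was sized. The size depends on assumed correlations: type I error is 5% if correlation is constant, about 8% to 18% under AR(1) of 0.5 to 0.95 per fortnight with seven scores, and about 7% to 10% with the three clinic visits. Constant correlation is the less plausible end for a fluctuating symptom score, but the article offers no data to settle it.

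The averaged-effect reading is a secondary risk. Power is about 58% to 71% under a linear rise, and above the planned 80% if the effect comes early. The sample size of 52 per group is correct on its own inputs and is not in question. This is an inexpensive improvement to the primary analysis and does not invalidate the design.

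**What to change.** State the primary contrast as the between-arm difference in mean ACQ6 at 30 weeks. Estimate it from a model of the post-baseline scores with treatment by categorical visit, baseline ACQ6 and the randomisation strata (asthma severity and body mass index). Replace the random intercept alone with an unstructured within-woman covariance, or a lag-dependent one such as heterogeneous Toeplitz if the unstructured model does not converge. Say whether the telephone scores enter. The same covariance wording can serve the blood results.

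The cost is a change of wording, a few more covariance parameters and a small loss of degrees of freedom. SPSS, the package the article names, can fit such a model through its repeated-effects covariance. No extra women are needed: on the plan's inputs the week-30 change at 52 per group keeps 80.1% power at a 5% level. The trial status is given as not yet recruiting, so the change can be made before any data exist.
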